## **METHODOLOGY**

This study is a prospective, single-arm, non-randomized clinical trial to compare a mobile physical device linked to telemedicine with traditional physical examination in the care of patients in the emergency department of a pediatric hospital.

## **RESEARCH LOCATION**

This study was performed in two pediatric, tertiary care and high complexity hospital (Pequeno Príncipe Hospital and Sabará Hospital), located in Curitiba and São Paulo, respectively.

## **STUDY DESIGN**

This study will perform in two steps. The first is the integration of the Tytocare® system with the hospital's electronic system, to enable the operationalization of telemedicine technology. This step will not include patients and will conduct an estimated time of two to four months to complete. The second step refers to patient care through telemedicine, using the Tytocare® medical device

and the teleinterconsultation modality, that is, from doctor to doctor. This step will include 698 patients with Informed Consent Form and with an estimated time of ten months.

1. Integration of the Tytocare operating system with the electronic system for telemedicine feasibility

This step will not include patient participation. This step will allow the data and images generated by Tytocare® to be sent to the hospital's electronic system. The data captured will be transmitted to the devices and, through the Tytocare® system, will be stored in a database hosted in a “cloud”, where the security and integrity of the data will be guaranteed by Tytocare®. Once stored in the Tytocare® system, it will be necessary to develop a system to allow interoperability between the Tytocare® system and the Hospital's electronic system. Through the Web Service layer, data will be retrieved from the Tytocare system database by the electronic system, and insert into the patient's medical record as the care steps begin, following safety rules access and persistence of the system.

It is important to highlight that data security and integrity will be guaranteed at four different times: a) on the capture device; b) in the traffic from that to the Tytocare system; c) from this to the patient's medical record system; d) and in the medical record system.

2. Patient care using Tytocare® in the emergency room through teleinterconsultation

The objectives of this step will be to enable teleinterconsultation between physicians, using Tytocare®, as well as to compare the data from the physical examination obtained by Tytocare® versus the data from the physical examination performed in a traditional way, by the physician in a routine consultation, as diagnostic support.

## PARTICIPANTS

Eligible participants in this study will be those classified as low risk (classified as green) in the triage performed by nurses in the emergency room.

Both hospitals have a risk classification protocol to stratify and classify all patients who arrive at the Emergency room. This classification is performed by the nurse and the protocol consists of five color codes (red, orange, yellow, blue and green):

- Red: serious patient, considered as an emergency, with immediate care;
- Orange: patient considered urgent, with care within a maximum period of 15 minutes;
- Yellow: patients who do not present conditions that characterize medical urgency, however, are identified as patients who require particular conditions for prioritization. As those who have comorbidities, associated with clinical conditions with potential risk for complications, with a goal of care of up to one hour;
- Green: patients who do not present clinical conditions that characterize medical urgency, with an average time of care within four hours;
- Blue: patients who have specific needs for procedures. These patients will not be classified because they do not have clinical circumstances, but they will be prioritized over those classified as non-urgent (Green), such as: tube replacement, administration of medication or dressings. Your average handle time target is two hours.

## ELEGIBILITY CRITERIA

### Inclusion criteria:

Will be eligible:

- Patients from 0 to 18 years old;
- Patients of both sexes;
- Patient treated in the Emergency Service of the public and private system;
- Patients classified in the green code (low risk) in the screening perform in Emergency Care;
- Patients in which one of the parents or legal guardian consents and signs the Informed Consent Term.

### Exclusion criteria:

- Patients classified in red, orange, yellow and blue codes;

- Patients in which the legal guardian or one of the parents does not consent to participation;
- Patient who does not agree to sign the Term of Assent/consent.

## FLOWCHART OF THIS STUDY

The single-arm, non-randomized clinical trial in second step will consist of selecting patients classified as code green (low risk), who will undergo two medical consultations and two physical examinations (Tytocare® and traditional), with the aim of comparing the results between these two modalities of examination and diagnosis. The flowchart will be as detailed in the steps below and illustrated in figure 1.

[figure not shown]

Figure 1. Flowchart of patient consultations in the study.

**Step 1:** The patient, after going through the nursing screening and being classified as code green and accepting to participate in the study, will be submitted to the first consultation with Tytocare® intervention, in the room 1. This consultation will be performed by a pediatric resident of the first year, whose inexperience should mimic that of the non-specialist doctor in the health units. The resident will collect information related to past medical history, current symptoms, and will perform a physical examination using Tytocare®. This device allows obtaining the following finding: heart rate, respiratory rate, body temperature, cardiac, pulmonary and abdominal

auscultation, otoscopy and oroscopy. In this room, Tytocare® and an attached computer will be available for data recording by the Pediatrics Resident.

**Step 2:** As the data is entered into the computer, it will be transmitted from the Tytocare® platform to the electronic system, and a second physician, called PEDIATRICIAN 1, will receive the results and images of the physical examination obtained by Tytocare®. PEDIATRICIAN 1 will be allocated in a room, called the situation room, guiding the resident and confirming the patient's care, thus configuring a second opinion on the case, thus characterizing the teleinterconsultation. These two doctors will decide together at a diagnostic hypothesis, diagnosis and/or course to be taken, which will be recorded in the data collection form (electronic document in the electronic system).

**Step 3:** The patient will be invited to go to the second consultation, which we will call a traditional consultation, and will be performed by another pediatrician, called PEDIATRICIAN 2. In this consultation, the doctor will perform the entire routine procedure (anamnesis with physical examination), without the use of Tytocare®. The traditional physical examination consists of obtaining the same clinical parameters using usual means or equipment such as a digital thermometer, sphygmomanometer, stethoscope and otoscope. This second consultation will take place in the hospital's emergency medical office, according to the service's demand flow. This physician will record your finding (vital signs, diagnostic hypothesis and conducts) on a patient registration form in the electronic system. In this moment, PEDIATRICIAN 2 will not have access to information registered for PEDIATRICIAN 1, in order to not compromise the results.

**Step 4:** The PEDIATRICIAN 2 will decide and communicate the diagnosis to the parents. Your conduct and/or diagnosis and treatment proposal will perform.

If there is a divergence between diagnoses, this will be observed in real time by the study coordinator and, in order to ensure patient safety, PEDIATRICIAN 2 can consult and discuss with the resident and PEDIATRICIAN 1. Furthermore, the PEDIATRICIAN 1 can use the results and images from the Tytocare® physical examination, however, without being able to make changes to the information in the data collection document.

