#### DATA COLLECT

Data collection will perform through an electronic document in the electronic system at the study hospital, specially prepared to collect and record research data. This document will present the following information about patient: general data (age, weight, comorbidities), clinical history, physical examination (heart rate, respiratory rate, temperature, blood pressure, cardiac, pulmonary and abdominal auscultation, otoscopy and oroscopy), diagnosis, diagnostic hypothesis and management.

The data collection instrument will be the same for the consultation with Tytocare and the traditional consultation. However, PEDIATRICIAN 2 will not have access to the PEDIATRICIAN 1 results registration form and vice versa, to ensure data confidentiality and research suitability.

A study coordinator will be able to access the two records, in order to see if there is a discrepancy between the diagnoses or diagnostic hypotheses. When this occurs, the coordinator will inform PEDIATRICIAN 2 if he wants to discuss the case with PEDIATRICIAN 1 and the pediatric resident who treated the patient with Tytocare®.

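### The protocol masks the written record but has no rule for what the family may carry by word of mouth from the device consultation to PEDIATRICIAN 2, so agreement may be inflated by an unknown amount

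*Combined protocol and SAP*

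**What the plan says.** The section on the study flowchart fixes the order. In Step 1 the patient "will be submitted to the first consultation with Tytocare": a first-year resident takes the history and examines the child with the device. In Step 2 PEDIATRICIAN 1 takes part from another room, "guiding the resident and confirming the patient's care, thus configuring a second opinion on the case", and the two agree a diagnostic hypothesis. Step 3 continues: "The patient will be invited to go to the second consultation, which we will call a traditional consultation". Its content is a complete consultation: "In this consultation, the doctor will perform the entire routine procedure (anamnesis with physical examination), without the use of Tytocare". Its timing is left open: "This second consultation will take place in the hospital's emergency medical office, according to the service's demand flow".

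Two sentences protect independence. Step 3 states: "PEDIATRICIAN 2 will not have access to information registered for PEDIATRICIAN 1, in order to not compromise the results". The section on data collection adds: "PEDIATRICIAN 2 will not have access to the PEDIATRICIAN 1 results registration form and vice versa".

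Step 4 bears on what the family may know: "The PEDIATRICIAN 2 will decide and communicate the diagnosis to the parents".

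**The concern.** The same parent or adolescent is the informant at both consultations, and the device consultation always comes first. If something said in room 1 is repeated to PEDIATRICIAN 2, information passes from the device assessment to its comparator, and never the other way. It can shape the second history and direct attention to an organ already described as abnormal. Masking the forms does not prevent this.

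The study's hypothesis is that the device examination, or a diagnosis supported by it, is equivalent to the traditional one, judged by paired proportions and agreement. A relay that PEDIATRICIAN 2 adopts raises kappa and removes discordant pairs, and both changes favour that hypothesis. A larger sample would not remove the effect. With no record of disclosure, it could not be assessed afterwards either.

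**Working it through.** **What each provision covers**

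- PEDIATRICIAN 2 reading what the first team registered: barred in Step 3.
- Either pediatrician opening the other's form: barred under data collection.
- The first team announcing a diagnosis: not barred, but Step 4 gives that task to PEDIATRICIAN 2.
- Findings spoken during the first examination, or in the exchange between the resident and PEDIATRICIAN 1: no rule.
- The family repeating any of this to PEDIATRICIAN 2: no rule, and no field to record it.

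**Inputs**

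- Kappa 0.3 against 0.4, alpha 0.05, power 80%, n = 698, from the section on concordance. The text calls 0.3 and 0.4 proportions; read as kappa values they reproduce the table.
- Discordant proportions 0.05 and 0.10, n = 468, from the section on paired proportions.
- Two-sided testing and, for kappa, marginals of 0.5: not stated, assumed here because they reproduce the plan's figures.
- Share of families disclosing, L = 10%, 20%, 30%, taken as the same among pairs that would otherwise disagree; share of disclosures adopted, a = 100% or 50%. The documents give neither, so both are assumptions.

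**Step 1: the plan's own figures.** With both marginals at 0.5 the large-sample variance of kappa is (1 − k²)/n, so

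n = [1.96·√0.91 + 0.842·√0.84]² / 0.10² = (1.870 + 0.771)² / 0.01 ≈ 697.5, rounded up to 698. This matches, as does 927 at 90% power.

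For McNemar, n = [1.96·√0.15 + 0.842·√(0.15 − 0.05²)]² / 0.05² gives 469 against the stated 468.

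**Step 2: effect on kappa.** Let c = a·L be the share of otherwise discordant pairs that become concordant. If the two methods have equal marginals, chance agreement is unchanged and observed agreement rises by c times the discordant share. Hence

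apparent kappa = k + (1 − k)·c.

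From k = 0.30:

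| L | All adopted (upper bound) | Half adopted |
|---|---|---|
| 10% | 0.30 + 0.70 × 0.10 = 0.37 | 0.30 + 0.70 × 0.05 = 0.335 |
| 20% | 0.44 | 0.37 |
| 30% | 0.51 | 0.405 |

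The plan's whole difference of 0.10 is reached at c = 0.10/0.70 = 14.3%. That is about one family in seven with full adoption, or two in seven with half adoption.

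**Step 3: what this does to the test at n = 698.** The probability of declaring kappa above 0.3 when it is truly 0.3 is Φ[(k′ − 0.3 − 1.96·√(0.91/698)) / √((1 − k′²)/698)], where k′ is the apparent kappa. It is 2.5% at c = 0, and about 16% at c = 5%, 49% at 10%, 80% at 14.3% and 98% at 20%.

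**Step 4: effect on McNemar.** If both discordant proportions shrink by the factor (1 − c), power for 0.05 against 0.10 falls as follows:

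- at n = 468, from 80% to 76% (c = 10%) and 71% (c = 20%);
- at n = 698, from 93% to 90% and 86%.

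**Step 5: which items are exposed.** The diagnostic hypothesis rests partly on the history, and auscultation, otoscopy and oroscopy depend on the examiner's judgement, so these are the most open to suggestion. Temperature and other instrument-read items are less so. A remark about an ear bears on otoscopy, not on heart sounds, so a single L for every item is a simplification.

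**The case against.** The strongest reply is that the documents show a possibility and not an effect. They do not say that the family hears the findings. PEDIATRICIAN 1 is in another room and receives data electronically, and how the two doctors confer is not described. Step 4 implies that the first team is not meant to announce a diagnosis, which partly protects the very outcome that would be most exposed. A pediatrician doing a full examination will not adopt every remark a parent makes, and a garbled relay could even produce disagreement. The consent documents and the flowchart figure were not available for this point and might carry an instruction to families.

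Most of this stands, and it rules out three stronger readings that a reader might infer:

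- That the family goes directly from one room to the other. The protocol gives no interval, only the demand on the service.
- That nothing at all limits disclosure. Step 4 does so in part.
- That PEDIATRICIAN 2's assessment is therefore shown not to be independent. No disclosure or adoption rate is given, so only a risk of unknown size is supported.

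The gap itself remains. Step 4 assigns a task and forbids nothing. It concerns the diagnosis only, while individual findings are also compared. The protocol restricts access to records expressly so that results are not compromised, and that purpose applies equally to the spoken route.

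**Conclusion.** The point holds as a risk that the protocol leaves open. Masking covers records, the order is fixed, the informant is the same, and no stated rule covers what was said in room 1. Agreement on the diagnostic hypothesis and on subjective findings may be inflated.

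The size is unknown. The figures of 0.37, 0.44 and 0.51 are upper bounds for the assumed disclosure rates: they require every disclosure to be adopted, equal marginals, and disclosure unrelated to whether the pair would have disagreed. They are not estimates. They do show that modest carry-over is comparable with the 0.1 difference in kappa on which the 698 rests, which justifies an inexpensive safeguard. The coordinator-prompted discussion of diverging diagnoses is a separate route and forms no part of this point.

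**What to change.** - **Steps 1 and 2.** State that the resident and PEDIATRICIAN 1 confer out of the family's hearing, for example by headset or chat. They do not tell the family the findings or hypothesis until PEDIATRICIAN 2's record is saved. State also that this does not limit any communication needed for the child's safety.
- **Step 3.** Add one field in which PEDIATRICIAN 2 records whether the family mentioned anything from the first consultation, and which item it concerned.
- **Analysis.** Report the disclosure rate overall and by item. Give agreement excluding disclosed pairs only as a secondary sensitivity analysis, with item prevalence shown for both sets. Families are likely to repeat positive findings more often, so exclusion may remove positives selectively and change kappa for that reason alone. The difference between the two results should not be read as the carry-over effect.

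The cost is one instruction, a headset or chat channel and one form field, with no extra staff or visits. The downsides are a slightly less open first consultation and a sensitivity analysis on fewer, possibly selected, pairs.

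### Device exam always first, traditional exam later by another doctor at an unrecorded interval: sign-level disagreement mixes device, time and examiner effects

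*Combined protocol and SAP*

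**What the plan says.** Under FLOWCHART OF THIS STUDY, Step 1, every enrolled child "will be submitted to the first consultation with Tytocare® intervention, in the room 1". That consultation is "performed by a pediatric resident of the first year, whose inexperience should mimic that of the non-specialist doctor". In Step 2 a remote pediatrician (PEDIATRICIAN 1) receives the device output and guides the resident, and "These two doctors will decide together at a diagnostic hypothesis".

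In Step 3 the traditional consultation follows and "will be performed by another pediatrician, called PEDIATRICIAN 2". Its timing is left to the department: "This second consultation will take place in the hospital's emergency medical office, according to the service's demand flow". No maximum gap is stated, and the order is not varied. The only time figure that bears on the wait is in PARTICIPANTS, where green-code children are described "with an average time of care within four hours".

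DATA COLLECT lists general data, history, examination findings, diagnosis and management. It lists no time of either examination, no interval and no treatment between the two. Step 3 and DATA COLLECT keep the two pediatricians masked to each other's forms.

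The analysis, in SAMPLE SIZE AND STATISTICAL ANALYSIS and ANALYSIS OF RESULTS, consists of paired proportions (McNemar) and kappa. It has no term for time, order or examiner. The hypothesis is that the device examination, or the diagnosis it supports, is equivalent to the traditional one.

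**The concern.** In every pair, four things change together: the method, the position in the sequence, the clock time and the examiner. A child's temperature, heart rate, respiratory rate or chest signs may differ at the second examination because the child has changed. They may also differ because another doctor, with different experience, is looking. McNemar and kappa see only that the two entries differ, and the plan reads that difference as a property of the device.

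The error can go either way. A device with no error of its own could appear to disagree with the traditional examination. A real device difference could also be offset by a time or examiner effect in the opposite direction and pass as equality. Without the interval in the data, the part due to elapsed time cannot be examined afterwards.

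**Working it through.** **1. The plan's own figures.** Two-sided alpha 0.05 (z = 1.960) and power 0.80 (z = 0.842); sidedness is not stated, but two-sided reproduces the figures.

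- Kappa 0.3 against 0.4, two categories, prevalence 0.5 assumed so that the variance term is 1 − κ²: N = [(1.960·√(1 − 0.09) + 0.842·√(1 − 0.16)) / 0.1]² = 697.5, which rounds up to the stated 698.
- McNemar with discordant proportions 0.05 and 0.10: N = [(1.960·√0.15 + 0.842·√(0.15 − 0.05²)) / 0.05]² = 468.6, against the stated 468.

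Both reproduce. The sample size is not what is in question.

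**2. How few one-way changes McNemar would read as a device difference.** Assume a perfect device, 698 pairs, and a symmetric background of b discordant pairs each way from other causes. Add k children whose sign changes in one direction between examinations. The exact two-sided p is 2·P(X ≤ b), with X ~ Binomial(2b + k, 0.5). The background levels are assumptions. The highest, 5% each way, equals the smaller of the plan's two discordant proportions.

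| Background each way | Smallest k with p<0.05 | Share of 698 | Split | p | p with one fewer |
|---|---|---|---|---|---|
| 0 | 6 | 0.9% | 6 vs 0 | 0.031 | 0.063 (5 vs 0) |
| 7 (1%) | 11 | 1.6% | 18 vs 7 | 0.043 | 0.064 (17 vs 7) |
| 35 (5%) | 20 | 2.9% | 55 vs 35 | 0.045 | 0.056 (54 vs 35) |

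With 5% background, 6 one-way changes give 41 vs 35, p = 0.57.

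**3. Effect on kappa.** Assume again a perfect device, with the sign present in 50% of children at the first examination. None of these inputs is in the documents.

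- Change only: if 10%, 20% or 30% of positive signs resolve before the second examination, kappa is 0.90, 0.80 or 0.70. For 20%: observed agreement 0.90, chance agreement 0.5·0.4 + 0.5·0.6 = 0.50, so kappa = (0.90 − 0.50)/(1 − 0.50) = 0.80.
- Examiner error only: with both examiners at 95% sensitivity and specificity, kappa is 0.81; at 90%, 0.64.
- Both, with 90% examiners and 20% resolution: kappa 0.51, discordance 16.2% vs 8.2%. McNemar at 698 pairs is then significant about 99% of the time. At 30% and 10% prevalence, kappa is 0.50 and 0.32.

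**4. Biases that cancel.** Give the first examiner 80% sensitivity and the second 90%, with 90% specificity for both. With no change in the child, discordance is 8.5% vs 13.5%, and McNemar is significant about 80% of the time. Add 10% resolution and discordance becomes 11.7% vs 12.7%. Two separate biases then look like near-equality.

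**The case against.** The strongest reply is that the examiner difference is intended. The resident stands in for a non-specialist, the modality is defined as doctor to doctor, and separate pediatricians are what make the masking possible. For the diagnosis comparison this stands: the resident plus PEDIATRICIAN 1 is the package under test. It does not cover the sign-by-sign comparison, which the plan also makes and states as a claim about the device examination.

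Second, noise from time and examiners lowers agreement and so works against the equivalence hypothesis. That is largely true of random change and error. It does not hold for directional effects, which can cancel, as step 4 of the working shows.

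Stronger readings are tempting, and the documents do not support them:

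- A reader might take four hours as the gap between examinations. It is an average time of care for the triage category, and the device consultation may use part of the same wait. The gap is unknown and could be short.
- A reader might infer that children mostly settle, or are treated, between examinations. The documents state neither. Treatment is described only after the second examination, in Step 4.
- A reader might conclude that six changed children would be enough to fail a perfect device. That needs no discordance at all in the opposite direction, hence faultless examiners as well. With 5% background each way, about 20 are needed.

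Rotating pediatricians between the two roles would not separate examiner from method, because the resident would still handle every device examination.

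**Conclusion.** The concern holds for the sign-by-sign comparison. With a fixed order, a gap set by demand and not listed for recording, and different examiners, the planned analyses cannot separate device disagreement from change in the child or from examiner differences. It does not hold in the same way for diagnosis, provided the result is read as a comparison of pathways.

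The documents give neither the size nor the direction of the effect. The range of 6 to 20 net one-way changes (0.9% to 2.9% of 698) rests on a perfect device and on assumed symmetric background discordance of 0% to 5% each way. The kappa figures rest on assumed prevalence, accuracy and resolution rates. They show that modest time and examiner effects could matter, not that they will occur. The trial remains feasible and the pathway comparison interpretable; what lacks support is a sign-level conclusion about the device alone.

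**What to change.** 1. **Record the interval.** Time-stamp both examinations automatically, and record any medication given in between. Keep the all-pairs analysis. Add a pre-specified analysis of sign agreement and paired differences by interval, for example a regression on the interval reported at interval zero. This addresses elapsed time only. The interval is not randomised, the value at zero may be an extrapolation, and examiner differences remain.
2. **Word the conclusion to match the design.** State it as the teleinterconsultation pathway (resident, device and remote pediatrician) versus an in-person pediatrician. Do not attribute sign-level differences, or their absence, to the device alone.

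The cost is two or three data fields, a little more analysis and a narrower device claim. Sample size, patient flow and masking are unchanged. The times need to be captured prospectively, since they may not be recoverable later.
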